### Who will take informed consent? {26a}

Following Institutional Review Board (IRB) and Health Insurance Portability and Accountability Act (HIPAA) guidelines, trained research staff will obtain informed consent from parents (for minor participants age 12–17) or adult participants (age 18–21 years) and assent from minors. Informed consent will be obtained at the clinical interview (Gate B), prior to data collection. If any minors turn 18 during their participation, they will be re-consented as an adult.

### Additional consent provisions for collection and use of participant data and biological specimens {26b}

Participants can optionally consent to (1) the storage and usage of their identifiable videos for future research related to mental health disorders and (2) the submission of their deidentified data to the National Institute of Mental Health Database (NDA) and the National Institutes of Health (NIH).

## Interventions

### Explanation for the choice of comparators {6b}

rTMS protocols involving both “inhibitory” pSMA stimulation and “excitatory” left dlPFC stimulation have demonstrated safety and clinical benefits in adult OCD, [25] but these have not yet been examined in the same study or tested in youth with OCD. We selected TBS stimulation protocols because these have been shown to be safe and tolerable in children, involve a brief duration of stimulation (2–3 min), and can be applied with lower stimulation intensity than conventional rTMS protocols [29]. Sham stimulation acts as a placebo comparison for active TMS conditions.

## Intervention description {11a}

Participants will receive 12 treatment sessions, delivered daily on consecutive weekdays. The first and twelfth sessions will be ERP orientation and relapse prevention sessions, respectively. Treatment sessions 2–11 will involve TMS immediately followed by ERP (Fig. 2). The number and timing of sessions was designed to ensure delivery of a full course of efficacious ERP [3, 4] alongside daily TMS, which is linked to long-lasting neural and behavioral change [30].

**Fig. 2 Fig2:**
[figure not shown]
Flow chart of treatment sessions

### TMS protocol

Both sites will use the Magstim Super Rapid2 stimulator (Magstim Company Ltd, UK) with a Magstim air-cooled 70-mm figure-eight coil for motor threshold determination and active TMS delivery. The Magstim sham air-cooled coil will deliver sham stimulation. This coil appears and sounds identical to an active coil but delivers a minimal portion of the magnetic field (< 3%). Stimulation intensity for all treatment sessions will be based on the resting motor threshold (RMT) obtained at the second treatment session, prior to the first TMS intervention session. Single-pulse TMS will be administered to the contralateral hand area of primary motor cortex to obtain the RMT, defined as the minimum intensity setting that elicits a threshold electromyography (EMG) response (≥ 50 mV in peak-to-peak amplitude) in a target muscle (abductor pollicis brevis) at rest in 5/10 trials.

The TMS coil placement will be individually determined using an automated neuroimaging analysis pipeline modeled after Lynch et al [31]. This pipeline integrates information about brain anatomy (structural MRI images), resting-state functional connectivity network maps (fMRI), and the modeled TMS-induced electric field (finite element method within the SimNIBS toolbox [32]) to output the coil location (*x, y, z* coordinates) for left dlPFC and pSMA targets. Coil orientation will be held constant for ease of administration. Coil placement will be guided by a stereotactic neuronavigation system (BrainSight 2.3.5, Rogue Research, Montreal, Quebec, Canada) using individual anatomical MRI data.

TMS parameters are as follows: (1) cTBS protocol: bursts of 3 pulses at 30 Hz repeated every 200 ms (5 Hz burst frequency), single uninterrupted 40 s train, 600 total pulses at 90% resting motor threshold (40 s duration); (2) iTBS protocol: bursts of 3 pulses at 30 Hz repeated every 200 ms for 2 s (1 train), trains repeat every 10 s (8 s inter-burst interval between trains), 600 total pulses at 70% resting motor threshold (190 s duration); (3) sham protocol: to enhance masking, half of sham participants will be exposed to the cTBS sequence and half will be exposed to the iTBS sequence.

### ERP protocol

ERP delivery will follow a principle-based treatment manual adapted from the POTS trials [33, 34] and tested in intensive (daily) formats [35]. The manual includes developmental adaptations to tailor delivery for different age groups. This manual was designed to incorporate exposure into each of sessions 2–11 and to maximize therapist delivery factors contributing to successful response prevention during exposures [6, 36]. All exposures will be conducted in-office to ensure that they can be captured on video for Exposure Process Coding System (EPCS) coding [6, 36] while maintaining privacy.

### Criteria for discontinuing or modifying allocated interventions {11b}

If needed, TMS stimulation intensity may be adjusted following review by a study physician. Participants may be withdrawn by investigators for any of the following reasons: (1) significantly deteriorating clinical course (e.g., acute suicidality); (2) significant adverse reaction to TMS; (3) serious physical illness; (4) significantly interfering non-compliance with study procedures; or (5) the participant no longer meets inclusion criteria. Participants will be free to decide to withdraw at any time for any reason. Study withdrawals will be documented, and we will make every attempt to conduct the remaining assessments and provide referrals when needed.

### Strategies to improve adherence to interventions {11c}

Coil placement during TMS administration will be continually monitored using BrainSight (BrainSight 2.3.5, Rogue Research, Montreal, Quebec, Canada). All ERP sessions will be video recorded and 100% will be coded using the Exposure Process Coding System (6) to measure compulsions and therapist and patient adherence. Participant compliance with ERP assignments and in-session tasks will be tracked by the ERP therapist at each session.

### Relevant concomitant care permitted or prohibited during the trial {11d}

To increase external validity of findings, we will include participants taking psychotropic medications that meet the study stability criterion and individuals who previously received OCD-specific therapy if they meet the OCD severity criterion. Concomitant psychotherapy is allowable if it is not focused on OCD. Participant medications and treatments will be checked daily prior to each treatment session. Any change will prompt principal investigator and/or physician review. Prior medications and psychotherapy will be recorded.

### Provisions for post-trial care {30}

The study will not include specific provisions for ancillary or post-trial care. Relevant treatment recommendations and referrals will be provided if participants/caregivers ask or if licensed clinical staff think the participant would benefit from additional clinical care.

### Outcomes {12}

Study assessment measures are listed in Table 1.

**Table 1 Tab1:** Study assessment measures and procedures

Assessment/Procedure	Purpose	Reporter	Administration Time						
			**Gate A**	**Gate B**	**Gate C**	**Sessions**	**Mid-Tx**	**Post-Tx**	**1-Month**
Phone screen	Initial Eligibility	Pa, Pt	x						
TMS/MRI-Safety Screen [51]	TMS and MRI safety	Pa, Pt	x						
Medical records	Current medications, relevant documents	SS	x						
Informed consent	Informed consent	–		x					
Concomitant treatment	Medication and therapies tracking	SS		x	x	x		x	x
Demographics	Sample characteristics	Pa, Pt		x					
Tanner Stage	Development	Pt		x					
DIAMOND-Kid [52]	DSM-V diagnoses	IE		x					
Children’s Yale-Brown Obsessive Compulsive Scale (C/YBOCS) [53]	OCD symptom severity, subtype	IE		x	x		x	x	x
Clinical Global Impressions (CGI) [54]	Global severity/improvement	IE		x	x		x	x	x
Ask Suicide-Screening Questions (ASQ) [55]	Suicidal ideation	Pt		x	x	x		x	x
Functional Magnetic Resonance Imaging (fMRI)	TMS targeting, RSFC outcome	–			x			x	
Neurocognitive tasks	Cognitive function	Pt			x		x	x	
Masking Questionnaire	TMS masking adequacy	Pa, Pt, SS						x	
TMS Adverse Events Questionnaire (AEQ) [56]	Side Effects/Adverse Events	Pt, SS				x		x	x
Client Satisfaction Questionnaire (CSQ-8) [57]	Treatment Satisfaction	Pa, Pt						x	x
Exposure Process Coding System (EPCS)* [28]	Compulsions; ERP Fidelity	SS				x			
Child Sheehan Disability Scale (CSDS) [58]	Impairment	Pa, Pt			x			x	x
Revised Children’s Anxiety and Depression Scale (RCADS) [59]	Anxiety/Mood	Pa, Pt			x			x	x
Behavior Rating Inventory of Executive Function (BRIEF) [60]	Executive Functioning	Pa, Pt			x			x	x
PROMIS Sleep Disturbance short form [61]	Sleep	Pt			x			x	x
Generalized Anxiety Disorder (GAD-7) [62]	Anxiety	Pa, Pt			x			x	
Patient Health Questionnaire (PHQ-9) [63]	Health	Pa, Pt			x			x	
WHO Disability Assessment Schedule (WHODAS-2) [64]	Functioning	Pa, Pt			x			x	
Menstrual Cycle	Cycle phase	Pt		x	x			x	x

*Pa* parent, *Pt* participant, *SS* study staff, *IE* independent evaluator

#### Phase 1

Primary outcomes focus on neural change and will be indexed by within-subject (pre- to post-treatment) and between-subject (iTBS vs. sham; cTBS vs. sham) change in fMRI-measured RSFC between the targeted network (pSMA-DLS for cTBS arm, dlPFC-DMS for iTBS arm). We will also examine several other outcomes. First, we will evaluate between-subject differences in compulsions during ERP (rate per session as observed by independent raters using EPCS). We will assess safety at baseline, post-treatment, daily treatment sessions, and 1-month follow-ups using the staff-administered Adverse Events Questionnaire (TMS AEQ), aggregated as the number of treatment-related adverse events and tolerability ratings of side effects. We will assess feasibility at post-treatment, based on treatment completion rate (percent of participants completing ≥ 80% of treatment sessions).

#### Phase 2

The primary outcomes are neural change (RSFC in the targeted circuit as in Phase 1) and change in compulsion rate (rate per session as in Phase 1). These will be indexed by within-subject (pre- to post-treatment) and between-subject (active vs. sham) change. We will also examine whether changes in neural and behavioral outcomes mediate change in OCD symptom severity (percent change in C/YBOCS total score from pre- to post-treatment). Secondary analyses will examine (1) the relationship between pre-treatment clinical measures and OCD symptom change, and (2) subgroup effects in primary outcomes, and (3) durability of change in primary outcomes through 1-month follow-up.

### Participant timeline {13}

Participant activities are depicted in Fig. 1. Participants who meet initial eligibility criteria on the phone screen (Gate A) will be scheduled for the clinical interview (Gate B), at which time the consent/assent and Gate B measures will be completed and final eligibility determined. The baseline assessment (Gate C), which involves the pre-treatment MRI scan, will be completed within 1 calendar month of Gate B. The daily treatment sessions will begin within 5 calendar days of completing Gate C (to allow for running and checking the TMS targeting pipeline). Participants will complete the 12 TMS + ERP treatment sessions (Fig. 2) within 15 business days. The mid-treatment assessment will occur between sessions 6 and 7. The post-treatment assessment will be completed within the 10 calendar days following the last treatment session, with a targeted window of 1–3 business days. The post-treatment MRI scan will occur at least 24 h after the last TMS session to avoid capturing the acute aftereffect of TMS. The 1-month assessment will be completed 4–6 weeks after the last treatment session.

### Sample size {14}

Power analyses for our sample sizes (phase 1 = 60, phase 2 = 60), assuming an attrition rate of 10%, (phase 1 = 54, phase 2 = 54) were calculated. In Phase 1, we will have 80% power to detect medium-to-large effects for within- and between-subject changes in RSFC (Cohen’s d range 0.70 to 0.96) and for group differences in compulsion rate (η2 = 0.23). In Phase 2, we will have 80% power to detect medium-to-large effects for tests of group differences in RSFC and compulsion rate (Cohen’s *d* = 0.78) and for tests of RSFC and compulsion rate as mediators of OCD symptom change (η2 range = 0.16 to 0.20).

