### Trial design {8}

Both phases are randomized, sham-controlled, double-masked, parallel-group, superiority trials. Phase 1 is a three-arm trial (sham, cTBS to pSMA, or iTBS to dlPFC; *n* = 20 per group), and phase 2 is a two-arm trial (sham or active stimulation; *n* = 30 per group; Fig. 1). Randomization in both phases will be blocked on site (Brown University or University of Minnesota) and symptom severity (Children’s or adult Yale-Brown Obsessive Compulsive Scale score above or below 32, indicating the cutoff for “extreme” symptoms). Participants have a 2 in 3 chance of being assigned to an active TMS treatment arm.

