##### Primary outcome (connectivity in targeted circuit)

Seed-based analyses [44] will test RSFC between a priori identified ROIs (as described above) and use a false discovery rate (FDR) correction for multiple comparisons threshold of *p* < 0.05. ROI correlation matrices will be converted to individual *Z*-scores using Fisher’s transformation, yielding indices representing RSFC in each targeted network. To test if active rTMS has a within-subject effect on RSFC, we will conduct paired *t*-tests for the change in RSFC for each active rTMS group within the targeted network (pSMA-DLS for cTBS arm, dlPFC-DMS for iTBS arm). We will conduct two separate two-sample *t*-tests for the group effect of rTMS: one for iTBS (dlPFC) vs sham and one for cTBS (pSMA) vs sham.

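### Several of the 80% power figures under Sample size {14} do not correspond to the planned analyses: Phase 1 RSFC ignores the FDR correction, the eta-squared values are not the thresholds for the 1-df tests, and none is power for mediation

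*Protocol article*

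**What the plan says.** Sample size {14} starts from 60 per phase, "assuming an attrition rate of 10%, (phase 1 = 54, phase 2 = 54) were calculated". For Phase 1 it states that "we will have 80% power to detect medium-to-large effects for within- and between-subject changes in RSFC", with Cohen's "d range 0.70 to 0.96", and the same power "for group differences in compulsion rate" at eta-squared 0.23. For Phase 2 it gives d = 0.78 for group differences in RSFC and compulsions, and eta-squared 0.16 to 0.20 "for tests of RSFC and compulsion rate as mediators of OCD symptom change". It names no test, degrees of freedom, alpha or multiplicity adjustment.

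The analyses are set out under Statistical methods {20a}:

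- **Phase 1 RSFC:** a paired t-test in each active arm and a two-sample t-test of each active arm against sham. The seed-based analyses are to "use a false discovery rate (FDR) correction for multiple comparisons threshold of" 0.05.
- **Phase 1 compulsions:** two linear regressions. The group indicator is the predictor of interest and total exposure duration is a covariate.
- **Phase 2 mediators:** percent change in C/YBOCS is regressed on group, the mediator and the group-by-mediator interaction. Exposure duration is added in the compulsion model.

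The Discussion describes Phase 2 as powered to establish how target engagement relates to OCD symptoms.

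**The concern.** A power statement should refer to the test that will be run, at the alpha that will be used. Three things do not line up here. The RSFC effect sizes look like uncorrected thresholds, while the analysis section corrects for multiplicity. The eta-squared values are larger than a single-coefficient test needs at these sample sizes, so either the df or the effect-size index is not what a reader would assume. The mediator figures are presented as power for mediation, yet mediation requires a treatment effect on the mediator as well as a mediator effect on the outcome.

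At stake is how results will be read, above all a null result. A null mediation finding in Phase 2 would look like the failure of a test with 80% power when its power was lower. A Phase 1 RSFC result that misses the corrected threshold would be misjudged in the same way.

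**Working it through.** **Inputs.** From Trial design {8}: "Phase 1 is a three-arm trial (sham, cTBS to pSMA, or iTBS to dlPFC", 20 per group, and "phase 2 is a two-arm trial (sham or active stimulation", 30 per group. With 10% attrition, Phase 1 has 54/3 = 18 per arm (36 for one active arm plus sham) and Phase 2 has 54/2 = 27 per arm. Alpha is not stated; two-sided 0.05 per test is assumed.

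**Formulas.** The t-tests use the noncentral t, with noncentrality d√n (paired) or d√(n/2) (two-sample). Regression tests use the noncentral F with u tested df, N − k − 1 error df for k predictors, λ = N·f² and f² = η²/(1 − η²).

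**Step 1: the d values reproduce, uncorrected.**

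| Test | d at 80% power, alpha 0.05 | Stated | d at 80% power, alpha 0.025 |
|---|---|---|---|
| Paired, n = 18 | 0.701 | 0.70 | 0.79 |
| Two-sample, 18 vs 18 | 0.961 | 0.96 | 1.07 |
| Two-sample, 27 vs 27 | 0.777 | 0.78 | not needed |

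**Step 2: Phase 1 RSFC under FDR.** The family is not defined, so it is taken here as the two arm comparisons of each type (Benjamini–Hochberg at 0.05, 40,000 simulated trials).

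| Scenario | Paired, d = 0.70 | Two-sample, d = 0.96 |
|---|---|---|
| Only one regimen effective | 70% | 70% |
| Both regimens effective | 77% | 78% |

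Alpha 0.025 is the strictest step for a family of two, so 0.79 and 1.07 are the largest detectable d values under that family.

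**Step 3: Phase 1 compulsions, N = 36, group plus exposure duration (k = 2).**

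- 1-df group test: f² = 0.231, so η² = 0.231/1.231 = 0.188.
- 2-df test of the whole model: η² = 0.227.
- 1-df test at alpha 0.025: η² = 0.222.

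The stated 0.23 agrees with the 2-df η² (0.227) or with the 1-df f² (0.231) labelled as eta-squared. It is not the 1-df η². If 0.23 is the group's own partial η², power is 89%. If it is a whole-model R² and group carries half of it, power for the group effect is about 61%.

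**Step 4: Phase 2 mediators, N = 54.**

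| Tested df | η² at 80% power | What it would correspond to |
|---|---|---|
| 1 | 0.131 | single mediator coefficient |
| 2 | 0.159 | mediator plus interaction |
| 3 | 0.179 | whole RSFC model |
| 4 | 0.196 | whole compulsion model |

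The stated 0.16 to 0.20 spans the 2- to 4-df tests. Read as partial η² of one coefficient, 0.16 to 0.20 gives 88–95% power.

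**Step 5: mediation.** Mediation requires both paths. The protocol's own d = 0.78 gives the treatment-to-mediator path 80% power. Requiring the mediator-to-outcome path as well can only lower that. Simulated joint-significance power at N = 54 (4,000 trials):

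| Mediator–outcome partial R² | d = 0.78, no interaction | d = 0.78, with interaction* | d = 0.5, no interaction |
|---|---|---|---|
| 0.13 | 61% | 39% | 33% |
| 0.16 | 67% | 46% | 38% |
| 0.20 | 74% | 55% | 42% |

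*Mediator coefficient as estimated in the sham-coded group.

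**The case against.** The strongest reply is that little power is actually lost and that the source of the eta-squared figures cannot be identified. Much of this stands.

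- **Origin.** A reader might infer that 0.23 and 0.16–0.20 are whole-model R² values. The document does not establish that. The 1-df f² at N = 36 also rounds to 0.23. With λ = f²(u + v + 1), v being the error df, the four-predictor compulsion model at N = 54 gives f² = 0.160 (1 df) and 0.197 (2 df), which is also the stated range. That convention then gives 0.238 rather than 0.23 for Phase 1 with its covariate, so no single convention settles the matter. A mislabelled f² would still make the stated eta-squared wrong.
- **Direction.** A reader might infer that the eta-squared mismatch means lost power. Read as partial eta-squared, the figures are conservative (88–95%).
- **Planned 2-df test.** The mediator and its interaction enter together, so 0.16 does fit one natural test of those terms.
- **FDR.** The family is undefined, and with both regimens effective the loss is only 2–3 points. All randomized participants are to be analysed with multiple imputation; as an upper bound, n = 20 per arm gives 76% at alpha 0.025 for d = 0.96.
- **Mediation.** The article describes regression terms and no test of an indirect effect, and the Discussion speaks of a relationship. But Sample size {14} says mediators, and 80% is not shown for that.

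It would also go too far to extend the point to compulsion differences in Phase 2. There d = 0.78 reproduces as an ordinary two-sample figure, although it leaves out the planned covariate.

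**Conclusion.** The point holds as a mismatch between the power statement and the analyses, in three parts.

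1. The Phase 1 RSFC values carry 80% power only without the prescribed correction. With FDR over two arm comparisons (assumed), power at those values is about 70–78%, depending on whether one or both regimens work.
2. The eta-squared values are not the 80% thresholds of the 1-df tests, which are 0.19 in Phase 1 and 0.13 in Phase 2. This is a mislabelled or differently defined quantity, not a demonstrated shortfall.
3. The 80% claim for mediation is not supported. On the protocol's own d = 0.78, power for both paths must fall below 80%. It is about 60–75% by a joint-significance test without the interaction and lower with it. These figures depend on the assumed paths and on a test the article does not name.

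A reader might infer that the decision to proceed to Phase 2 is compromised. It is not: the neural criterion in Objectives {7} is an effect size of at least 0.3, not a corrected p-value. Nothing here calls for a different sample size.

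**What to change.** Revise Sample size {14}; N and the planned tests stay as they are.

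- **Every figure:** state the test, tested df, alpha and effect-size index.
- **Phase 1 compulsions:** give partial eta-squared 0.19 for the 1-df group effect (N = 36), or say which df and index 0.23 refers to.
- **Phase 2 mediators:** give partial eta-squared 0.13 for a single mediator coefficient (N = 54), or say which tests 0.16 to 0.20 refer to. Describe this as power for the mediator–outcome association.
- **Mediation:** withdraw the 80% claim. If power for an indirect effect is quoted, give it as conditional, naming the test, both assumed paths and whether the interaction is in the model.
- **Phase 1 RSFC:** define the FDR family and give power after correction. For a family of two this is about 70–78% at d = 0.70 and 0.96, or detectable d of up to 0.79 (within arm) and 1.07 (between arms).
- **Discussion:** align the description of Phase 2 with the restated claim.

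The cost is a text amendment. The RSFC and mediation figures become less favourable; the detectable effects for the single-coefficient tests become smaller.

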### Recruitment {15}

Study information will be distributed to clinicians within the care systems of each site and across community practices in each region, focusing on those most likely to encounter individuals with OCD (i.e., psychiatrists, psychologists, primary care physicians). Advertising will occur via physical flyers posted in public spaces and digital flyers shared via lab social media accounts, departmental websites, and OCD-related patient support organizations. There will be separate recruitment for Phase 1 and Phase 2 of the randomized controlled trial (RCT).

### Assignment of interventions: allocation

#### Sequence generation {16a}

Block randomization, stratified on site (Brown or UMN) and baseline OCD severity (C/YBOCS total < 32 vs. > = 32), will be performed using the blockrand package in R [37].

